### Statistical analyses

We will use a MANCOVA to test for a significant treatment group (STRIPE vs SOC) main effect showing significantly greater improvement in each outcome variable at 6-week postintervention controlling for respective baseline values of each outcome variable. A multivariate intercept-only longitudinal SEM growth curve model will be used to determine if the difference in each outcome variable at 6-week postintervention is maintained at 6, 12, 18 and 24 months follow-up. The intercept-only SEM implies between-participant variability in the overall outcome variable, but the outcome does not change as a function of time. Finally, a binary logistic regression analysis will be used to determine if the intervention group (STRIPE vs SOC) significantly predicts PFP recurrence at the end of the 2-year follow-up. Dummy coded variables will be created and added to each analysis to account for cluster (site) differences and produce robust SEs. All missing data will be handled assuming MAR with maximum likelihood estimation consistent with currently accepted methodological research and practice.

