## Introduction

Patellofemoral pain (PFP) is one of the most common knee pathologies in the general population and military personnel.^1^ The incidence of PFP in the military ranges from 9.7 to 571.4 per 1000 person-years, with females at 2.2 times greater risk than males.^1 2^ The annual prevalence rate in the general adult population is 22.7%.^1^ PFP accounts for 7% of all diagnoses in patients who seek medical care^3^ and up to 25% of all treatment for knee-related injuries within sports medicine clinics.^4^ Persistent knee pain, disability and impaired joint-related and health-related quality of life are common in individuals with PFP.^5 6^

The aetiology of PFP is unknown. Increased stress on the patellofemoral joint due to altered lower extremity mechanics is proposed to be the primary mechanism of PFP.^7^ Altered movement patterns are common in individuals with PFP during tasks, such as single-leg squat, stair ambulation and running,^8 9^ and are associated with greater knee pain and worse subjective function.^10^ Hip musculature is a major influence on the control of these lower extremity mechanics, and adults with PFP are 20%–28% weaker in hip strength when compared with asymptomatic adults.^11 12^

Clinicians prescribe strengthening exercises focused on weak gluteal muscles,^13 14^ which produces positive short-term outcomes but suboptimal long-term outcomes. Over 90% of patients with PFP report knee pain and symptoms greater than 15 years following initial diagnosis.^6^ While most patients with PFP seek medical care,^8^ over 60% are not satisfied with their knee function within 3 months of concluding treatment.^15^ Numerous studies targeting hip abductor strength produce minimal improvements,^16^ and hip strength gains are lost within months of concluding treatment.^16 17^

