### Secondary outcomes

Hip muscle function will be assessed with peak torque and RTD during isometric contractions for abduction and extension with a hand-held dynamometer (HHD) (ErgoFet HHD, Hoggan Scientific, Salt Lake City, Utah, USA). For each task, a participant will be positioned with the HHD and taken through a series of sub-maximal isometric contractions to allow for warm-up and acclimation. The warm-up will consist of contractions at 25, 50, 75 and 100% of their self-perceived maximal isometric contraction. Muscle function will consist of three 5 s maximal contractions with verbal encouragement. Participants will be provided with a 1 min rest period between trials and 3 min rest period between testing positions, with positions completed in a randomised order varied over sessions. We will collect an additional test trial if coefficient of variation is greater than 10% between the three peak isometric torque trials.^34^ We calculated inter-rater reliability of gluteal RTD (inter-rater ICC=0.66−0.78) and isometric hip strength (inter-rated ICC=0.83−0.88; intrarater ICC: 0.80−0.98) between the three site assessors during a training session. Hip muscle function will be collected preintervention and immediately postintervention.

The dynamometer will be calibrated before each testing session. Thigh and shank length will be measured in centimetres for the test limb. Hip abduction will be conducted in a side-lying position with the test limb positioned at 20° of hip abduction, slight external rotation and slight hip extension.^19^ The HHD will be placed on the lateral aspect of the limb, 5 cm proximal to the lateral epicondyle and secured with a stabilisation strap.^19^ A second stabilisation strap will be placed around the table and participant’s pelvis to minimise accessory motion. Hip extension will be conducted with the participant’s trunk on the table and their lower limbs off the table, with both the hip and knee at 90° of flexion. The HHD will be positioned against the treatment plinth and a stabilisation strap placed around the HHD and participant’s limb, aligned 5 cm proximal to the popliteal fossa. A second stabilisation trap will be positioned around the table and the participant’s pelvis to control accessory motion.

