Power analysis for the four postintervention (6, 12, 18 and 24 months) assessments was calculated with a Monte Carlo simulation involving 5000 replications of sample data using Mplus V.8.6 for the intercept-only structural equation model (SEM; growth curve model)^36^ assuming: (1) standardisation of all outcome variables at all time points, (2) *T*=five 6-month assessment time points (postintervention, 6, 12, 18 and 24 months follow-up), (3) all individual trajectories are horizontal but at different (intercept) levels, (4) randomisation results in equivalent groups, (5) intermittent missing outcome variable data will be MAR, increase every 6 months and monotonically from 1.1% at the first postfollow-up assessment to 9.1% at month 24 and (6) α=0.05 (two tailed). The dispositive power analysis question regarded statistical power levels to reject the treatment effect null hypothesis at various hypothetical sample sizes under the assumptions listed above. Power analysis results showed power would be >0.70 for any (intercept) effect size difference between STRIPE and SOC participants of d>0.55.

Power analysis for PFP recurrence was assessed with a binary logistic regression using the internal Monte Carlo simulation capabilities in Mplus V.8.6 assuming: (1) 50% of the STRIPE participants will have a PFP recurrence and 82% of SOC participants will have recurrence, (2) previous publications suggest PFP recurrence for SOC is 50%–90%,^6^ (3) MCAR missing data were included in the simulation and estimated to be 20% missing data in the outcome variable (PFP recurrence) and (4) α=0.05 (two tailed). Power analysis results showed power >0.80 if N=88 for analysis following missing data handling and the group (STRIPE vs SOC) term results in an OR>4.43.

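### The intercept-only growth model tests an average STRIPE–SOC difference over five waves; it cannot show whether the 6-week difference is maintained to 24 months

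*Protocol article*

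**What the plan says.** Under Statistical analyses, a MANCOVA tests the group difference at 6 weeks. A multivariate intercept-only growth curve model is then meant to determine "if the difference in each outcome variable at 6-week postintervention is maintained at 6, 12, 18 and 24 months follow-up". The next sentence describes that model: "The intercept-only SEM implies between-participant variability in the overall outcome variable, but the outcome does not change as a function of time".

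The second part of the Sample size section confirms the form. Five waves enter (postintervention, 6, 12, 18 and 24 months). The simulation assumes that "all individual trajectories are horizontal but at different (intercept) levels". The power question is rejection of one treatment-effect null, and the stated result is power above 0.70 for an intercept difference of d>0.55.

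The article states no slope, group-by-time term, wave-specific comparison or definition of maintenance.

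VAS, AKPS and single-leg-squat kinematics are scheduled at all six time points in Table 2. For hip RTD, Table 2 marks only baseline and postintervention, and the Secondary outcomes section agrees: "Hip muscle function will be collected preintervention and immediately postintervention". The Abstract, however, says neuromuscular function of the hips will be assessed at every postintervention time point.

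**The concern.** Whether a difference is maintained is a question about change in that difference over time. A model in which nothing changes over time has no parameter for such change, so maintenance enters as an assumption and cannot emerge as a result. The single group coefficient pools early and late waves, and a large early difference can carry it even if nothing remains at 24 months.

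Adding the 6-week MANCOVA does not help. A significant 6-week difference together with a significant five-wave average is what one would see under a lasting benefit, and also under one that has faded away.

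Pain and function are primary outcomes followed for two years, and the Discussion hopes to inform prescribing for long-term as well as short-term outcomes. A statement that the benefit lasts to 24 months would rest on a test that does not address it.

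**Working it through.** **Inputs from the protocol.** N=88, allocated 1:1 (44 per arm); two-sided α=0.05; five waves; d=0.55; missing data rising from 1.1% to 9.1% in the growth-model simulation; 20% missing in the recurrence calculation; baseline R²=0.20, given only for the 6-week outcome.

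**Assumed.** The within-person correlation (ICC) is not stated; I use 0.5–0.7. Differences are in units of the total SD, with complete data, equal variances and compound symmetry unless noted.

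**1. The plan's own figure.** For a two-mean comparison with SD 1, power = Φ(d/√(2/n) − 1.96), where n is the number per arm.
- n=44: 0.55/0.2132 = 2.58, power 0.732.
- n=41.8 (about 5.1% missing, the midpoint of 1.1% and 9.1%): 0.71.
- n=40 (about 9.1% missing): 0.691.

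This is consistent with the stated value above 0.70. The article does not say on which SD d is scaled, so this is a check for consistency only. The power figure is not the fault.

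**2. What the intercept coefficient estimates.** Under the assumptions above it is the plain mean of the five wave differences, with

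SE = √[(4/88)(1+4·ICC)/5] = 0.165 (ICC 0.5) or 0.186 (ICC 0.7).

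**3. Chance of a significant intercept effect when the true 24-month difference is zero.**

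| True difference at post, 6, 12, 18, 24 months | Mean | ICC 0.5 | ICC 0.7 |
|---|---|---|---|
| 0.55 fading linearly to 0 | 0.275 | 0.38 | 0.32 |
| 0.8 fading linearly to 0 | 0.40 | 0.68 | 0.58 |
| 1.0 fading linearly to 0 | 0.50 | 0.86 | 0.77 |
| 1.1 fading linearly to 0 | 0.55 | 0.92 | 0.84 |
| 0.55 at post only | 0.11 | 0.10 | 0.09 |

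Example, first row at ICC 0.5: 0.275/0.165 = 1.67; Φ(1.67 − 1.96) ≈ 0.38.

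**4. Constant versus vanishing.** A constant 0.55 has mean 0.55, the same as 1.1 fading to 0, so the formula gives the same power for both (0.92 and 0.84). A simulation of 1000 trials per scenario, fitted by maximum likelihood with the stated missingness, agrees. The intercept effect was significant in 0.916 (constant) and 0.917 (fading) of trials at ICC 0.5, and in 0.845 and 0.851 at ICC 0.7. In the fading trials the 24-month difference itself was significant about 6% of the time, close to its nominal level.

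**5. What a model with time could do.**
- Contrast of 24 months with postintervention: SE = √[2(1−ICC)·4/88] = 0.213 (ICC 0.5) or 0.165 (ICC 0.7). A loss of 0.8 is detected with power 0.96 or more. A loss of 0.55 is detected with power Φ(0.55/0.213 − 1.96) = 0.73 at ICC 0.5 and Φ(0.55/0.165 − 1.96) = 0.91 at ICC 0.7.
- 24-month difference alone, d=0.55, t-test:

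| Available at 24 months | No baseline adjustment | If R²=0.20 held at 24 months |
|---|---|---|
| 79–80 (9.1% missing) | 0.68 | 0.77 |
| 70 (20% missing) | 0.62 | 0.72 |

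**The case against.** **The model is not useless.** It is a sound test of an average difference over follow-up, its stated power reproduces, and recurrence has its own two-year logistic analysis. All of this stands. The fault lies only in the question the model is said to answer.

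**Misfit could expose false flat trajectories.** In the simulation, a test of the mean structure on 8 degrees of freedom rejected in 83%–100% of fading trials. Fit checks may also sit in a full protocol or SAP that is not shown. This softens the risk, but the article names no such check. A general fit test also reacts to time trends shared by both arms, so it would not isolate loss of the group difference.

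**The size depends on the scenario.** Figures of 77%–86% need a starting difference of 1.0, well above the 0.55 on which the trial is sized. From 0.55 the figure is 32%–38%, and for an effect at postintervention only it is 9%–10%.

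**Stronger readings that the document does not support.** A reader might infer that the plan will report a vanished benefit as lasting. No rule says that a significant intercept will be read as a benefit at 24 months. A reader might also take the Introduction's remark that "hip strength gains are lost within months of concluding treatment" as the authors' own forecast that the STRIPE–SOC difference will fade. That remark concerns hip strength after existing treatment, not pain, function or a between-group difference; fading gains in the SOC arm could even widen the gap. Nor does the article say that the difference is expected to be largest at postintervention. Finally, it cannot be said flatly that hip RTD has no follow-up data, because the Abstract implies otherwise.

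**Conclusion.** The concern holds as a mismatch between question and model. The article states the question, names the model and describes its restriction in consecutive sentences, so this is not a detail left to a SAP. A significant intercept effect supports an average difference across postintervention to 24 months and nothing about its persistence.

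The chance that a difference absent at 24 months still yields significance runs from about one in ten to more than four in five across the scenarios examined, and is about one in three when it fades from the design effect. These figures rest on an assumed ICC, compound symmetry and complete data. That constant and fading differences with equal means cannot be told apart does not depend on the ICC value, only on the coefficient being a plain average. With unequal variances or missing data it becomes a weighted average, and the same difficulty remains.

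The hip RTD schedule is a separate and smaller inconsistency.

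**What to change.** For the outcomes with follow-up data (VAS, AKPS, kinematics), fit categorical time, group and group-by-time, or free the group means at each wave within the SEM. Report the STRIPE–SOC difference with 95% CI at every wave. Define maintenance in advance, and base it on the 24-month difference together with the contrast of 24 months against postintervention. Keep the intercept-only estimate, labelled as the average difference over follow-up. If the authors prefer not to change the model, restate the aim as that average and make no claim of maintenance.

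The change affects analysis wording only; no new data or participants are needed. The price is precision. At 24 months alone, power for d=0.55 is about 0.62–0.68 without baseline adjustment, and 0.72–0.77 if the 6-week R² of 0.20 also held at 24 months, which the article does not claim. It may therefore fall below the stated 0.70, and the article should say so.

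Separately, reconcile the Abstract with Table 2 and the Secondary outcomes section on when hip RTD is measured. If Table 2 holds, RTD cannot enter the longitudinal model, and the reference to each outcome variable should be narrowed.

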### Primary outcomes

Pain will be measured with a VAS, quantifying the participant’s worst knee pain in the previous week. Pain will be assessed using a 10 cm line, with ‘no pain’ and ‘worst pain imaginable’ anchored on the left and right sides of the VAS, respectively. The distance between the left anchor and the participant denoted location will be measured as the worst pain score in the previous week. A change of 2 cm on a 10 cm VAS reflects the minimal clinically important difference in pain following treatment for patients with PFP.^33^ The VAS has fair to good test–retest reliability (Intraclass Correlation Coefficient (ICC)_(3,1)_ =0.56−0.83)) (1 week) and moderate concurrent validity (r=0.62 with AKPS and r=0.74 with Functional Index Questionnaire) in individuals with PFP.^33^ We will collect AKPS at baseline and all postintervention time points (table 2).

The AKPS is a 13-item questionnaire to assess self-reported knee function in patients with PFP. The AKPS ranges from 0 to 100 points, with lower scores representing greater knee disability. A 10-point change on the AKPS reflects the minimal clinically important difference in self-reported function following treatment for patients with PFP.^33^ The AKPS has good test-retest reliability (ICC _(3,1)_ =0.81) and moderate concurrent validity (r=0.70) with usual pain in the PFP population, and significant responsiveness.^33^ AKPS will be collected at baseline and all postintervention time points (table 2).

PFP recurrence will adhere to previously established methods^17^ and be assessed at four time points: 6, 12, 18 and 24 months following the intervention (table 2). Compensation will be provided to participants at each follow-up time point to improve retention. At each time point, participants will report if they experienced PFP in the previous 6 months and the average hours per week engaged in running or exercise in the previous 4 weeks.^17^ Recurrence will be defined as an event that requires treatment from a healthcare professional or being unable to participate in normal exercise for more than 2 days due to retropatellar or peripatellar pain.^17^ If additional clarification is required, follow-up will be completed with the research team member and participant through email.

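### The recurrence power statement claims 88 analysable outcomes where the stated logistic model would have about 70; the power figure stands, but reports from participants who leave early are not used

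*Protocol article*

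**What the plan says.** Recurrence is one of three primary outcomes (Protocol article, Aims and objectives). Under Primary outcomes it will "be assessed at four time points: 6, 12, 18 and 24 months following the intervention", and at each of these visits "participants will report if they experienced PFP in the previous 6 months". The event is then specified: "Recurrence will be defined as an event that requires treatment from a healthcare professional", or more than two days unable to do normal exercise because of the knee pain. A first recurrence can therefore be placed in a 6-month interval.

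Under Statistical analyses, the one model named for recurrence is a logistic regression asking whether treatment arm "significantly predicts PFP recurrence at the end of the 2-year follow-up". Site is covered by a general statement for all models: "Dummy coded variables will be created and added to each analysis to account for cluster (site) differences". Missing data are to be handled by maximum likelihood assuming missing at random.

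Under Sample size, the recurrence calculation takes 50% recurrence in STRIPE and 82% in SOC, two-sided alpha 0.05, and missing data "estimated to be 20% missing data in the outcome variable (PFP recurrence"). It reports "power >0.80 if N=88 for analysis following missing data handling" and an odds ratio above 4.43. For the growth-curve outcomes, the same section assumes 9.1% missing at month 24.

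The article does not say whether the binary outcome is any recurrence over two years or only the final report, or how someone who recurred and then left is coded.

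**The concern.** Two things do not fit together.

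First, the power statement treats missing-data handling as if it returned all 88 participants to the analysis. Maximum likelihood can use a participant with a missing outcome only if something else in the model carries information about that outcome. The model described has one outcome and two fully observed predictors, so nothing does.

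Second, four reports per participant are reduced to a single yes/no at two years. A participant who reports no recurrence at 6 and 12 months and then leaves contributes nothing. One who recurs at 6 months and then leaves is a known event under a cumulative definition. Keeping the second while losing the first tilts the observed sample towards recurrence; dropping both discards known events of a primary outcome. At stake are the accuracy of the arm-specific recurrence risks, a little power, and a correct statement of how much data the result will rest on.

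**Working it through.** **Inputs from the protocol.** 88 participants, 1:1, so 44 per arm; sites of 44, 22 and 22; recurrence 50% against 82%; 20% missing outcomes; two-sided alpha 0.05; threshold odds ratio 4.43.

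**1. The plan's odds ratio.** (0.82/0.18) / (0.50/0.50) = 4.56. Conversely, an odds ratio of 4.43 against 50% is a SOC risk of 4.43/5.43 = 0.816, which rounds to the stated 82%. The figures agree.

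**2. How many outcomes enter the model.** 0.80 × 88 = 70.4, or about 35 per arm.

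**3. Which N the threshold belongs to.** Two-proportion power with pooled variance under the null, n per arm:

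power = Φ{[|p2 − p1|√n − 1.96√(2p̄(1 − p̄))] / √[p1(1 − p1) + p2(1 − p2)]}

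With p1 = 0.500, p2 = 0.816 and p̄ = 0.658, the null term is 1.96 × 0.671 = 1.315 and the denominator is 0.633.

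- n = 35: (0.3158 × 5.916 − 1.315)/0.633 = 0.875, so power is 0.81.
- n = 44: (0.3158 × 6.633 − 1.315)/0.633 = 1.233, so power is 0.89.

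Exact enumeration of the logistic Wald test gives 0.808 and 0.895. A simulated logistic model with site dummies gives about 0.82 and 0.89. The smallest odds ratio with 80% power is about 4.41 at 70 outcomes and about 3.6 at 88. So 4.43 is the threshold for about 70 observed outcomes: the plan's figure is reproduced with the 20% loss included and not without it.

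**4. Bias if only known events are kept.** Assume a constant recurrence rate over the four intervals and 5% of participants leaving before each visit (neither is in the protocol). Cumulative risk at 6, 12 and 18 months is 0.159, 0.293 and 0.405 in STRIPE, and 0.349, 0.576 and 0.724 in SOC.

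- STRIPE: known events 0.80 × 0.50 + 0.05 × (0 + 0.159 + 0.293 + 0.405) = 0.443; known non-events 0.80 × 0.50 = 0.400; apparent risk 0.443/0.843 = 52.5%, against a true 50%.
- SOC: known events 0.80 × 0.82 + 0.05 × (0 + 0.349 + 0.576 + 0.724) = 0.738; known non-events 0.80 × 0.18 = 0.144; apparent risk 0.738/0.882 = 83.7%, against a true 82%.

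The overstatement is 2.5 and 1.7 points. The odds ratio barely moves: (0.738/0.144)/(0.443/0.400) = 4.63 against 4.56.

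**5. What the unused visits are worth.** Simulated power at the plan's 24-month rates with 20% dropout spread over visits:

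| Analysis | Constant hazard | Arms separate late |
|---|---|---|
| Logistic, 24-month completers | 0.81–0.83 | 0.82–0.84 |
| 24-month cumulative risk from all four visits | 0.84 | 0.86 |
| Discrete-time hazard or log-rank, all visits | about 0.90 | about 0.6–0.7 |
| Logistic, all 88 outcomes known | 0.90–0.91 | – |

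Late separation means equal risk in both arms early on, for example 30% by month 6 or 40% by month 12, with 50% and 82% still reached at month 24. Those early risks are assumptions. At 9.1% dropout and constant hazard, completers-only logistic has about 0.875 and the log-rank about 0.92.

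**The case against.** The strongest objection is that the loss was already allowed for. The simulation included 20% missing outcomes, and the threshold it returned is the one for about 70. This stands. A reader might infer from the wording about 88 that the trial is underpowered for recurrence; step 3 shows that it is not.

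A reader might also infer that the logistic model should give way to a hazard model. The documents do not support that. The hypothesis concerns recurrence rates over a two-year horizon, which a 24-month risk comparison addresses directly, and a hazard ratio would be a different estimand. Its extra power depends on roughly proportional hazards. The Introduction describes good short-term and poor long-term results of strengthening, with strength gains lost within months, so late separation is plausible, and there the hazard model loses power.

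It is also fair that an article may leave the coding of partial follow-up to the full protocol, and that maximum likelihood could be run jointly with the earlier reports. The coding bias is therefore conditional on a rule not shown. But the article names one outcome at one time point, and no joint model. A check in which dropout depended on earlier recurrence left the completers' odds ratio at 4.35 to 4.53 against about 4.55, although at the extreme the arm risks fell from 50% to 41% and from 82% to 75%.

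**Conclusion.** The stated analysable N is wrong for the stated model: about 70, not 88, given the plan's own 20%. The stated power is right and the sample size need not change. The logistic test is valid; it simply leaves collected data unused. Under constant hazard and evenly spread dropout, counting known events without the recurrence-free follow-up overstates arm-specific recurrence by about 2 to 3 points, with little effect on the odds ratio. A 24-month risk comparison drawing on all four visits avoids this and gains about 1 to 3 power points at 9% to 20% dropout, whether the arms separate early or late. The hazard model's gain, from about 0.81 to 0.90, is not assured: under late separation it becomes a loss, to about 0.6–0.7 against 0.84. This is worth correcting, but it does not threaten the trial's ability to answer the question.

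**What to change.** 1. In Sample size, state that power above 0.80 at an odds ratio of 4.43 rests on about 70 observed outcomes. Explain or reconcile the 20% missing recurrence with the 9.1% missing at month 24 for the growth-curve outcomes.

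2. In Statistical analyses, define the outcome as any recurrence within 24 months. Estimate cumulative 24-month risk by arm from all four visits, using a discrete-time life table or a likelihood or imputation model that includes the earlier reports. Each participant contributes until first recurrence or last contact. Compare the arms on 24-month risk, as a risk difference or odds ratio adjusted for site.

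3. State a rule for a missed intermediate visit. With a 6-month recall window, a missed visit leaves that interval unobserved even if the participant returns.

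4. If wanted, add a discrete-time hazard ratio as a secondary analysis, not as a replacement.

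The cost is some extra analysis work and the missed-visit rule. No new data or participants are needed, and the two-year risk remains the estimand.
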